## Abstract

**Background:**

Dental fear and anxiety (DFA) affects approximately a quarter of children and adolescents. It significantly contributes to pediatric patients avoiding dental care later in adulthood. Lack of cooperation due to DFA can create a stressful environment, often forcing dentists to end appointments prematurely and consider alternative pharmacological treatments. The use of virtual reality (VR) during dental procedures, offering an immersive sensory experience, may serve as an additional nonpharmacologic tool to better manage DFA in children with special health care needs (SHCN) undergoing dental treatment.

**Objective:**

This study aims to assess the effectiveness of VR immersion in reducing anxiety and pain among pediatric patients with SHCN undergoing dental procedures. The study also seeks to understand the satisfaction of parents and health care providers with the use of VR during dental appointments.

**Methods:**

This randomized controlled trial follows a parallel design with two groups: a control group receiving standard care and an experimental group using VR. A sample size of 400 participants was calculated. Participants will be randomly assigned equally to each group. Recruitment will take place at the dental clinic of the Centre Hospitalier Universitaire Sainte-Justine, a tertiary- and quaternary-care center that primarily serves pediatric patients with SHCN. The two primary outcomes will include both observed and objective biomarker-based measures of anxiety. DFA will be evaluated using the Venham Anxiety Rating Scale as well as changes in mean levels of salivary alpha-amylase. Sociodemographic characteristics, parents’ and health care professionals’ satisfaction levels, participants’ pain intensity and behavior during the procedure, changes in heart rate, occurrence of side effects, procedure duration, and any deviations from normal procedural length will also be collected. Descriptive and comparative statistics will be conducted for demographic and clinical comparisons and will be used to present sociodemographic and clinical data, parents’ and health care professionals’ satisfaction levels, child satisfaction with the game, and procedural time.

**Results:**

This study will be conducted from November 2023 to December 2025. As of November 2025, 300 participants have been recruited. Results are expected to be available in June 2026.

**Conclusions:**

We believe that the results of this study will confirm the efficacy of VR in reducing DFA in children with SHCN, providing an additional nonpharmacological alternative for better managing this condition in pediatric hospital settings.

## Introduction

### Background

Dental fear and anxiety (DFA) is defined as a patient’s psychological state of worry, anxiety, or even dread that is specific to a dental procedure [1]. Although different, dental fear and dental anxiety, which respectively represent an emotional response and a heightened state of apprehension to potential distress from dental treatment, are challenging to distinguish in clinical practice [2,3]. Consequently, the term “dental fear and anxiety” is frequently used to describe these intense negative emotional states associated with dental procedures. Children’s DFA disorder refers to the clinical manifestations of dental phobia or anxiety in children, including reduced cooperation, lessened compliance, and even resistance to treatment [4,5]. DFA are conditions that affect approximately 13.3% to 29.3% of children and adolescents and are a significant reason why patients avoid dental care [3,6]. In children, DFA is also associated with lower oral health-related quality of life [7]. Although the etiology of DFA is multifactorial, often stemming from both exogenous and endogenous sources, a past traumatic dental experience is the most predictive factor for DFA [8,9]. A study by Ten Berge et al [10] states that the majority of DFAs experienced by adults originates from poor dental experiences during childhood. These findings highlight the importance of making each dental visit a positive experience for pediatric patients. Short-term distress during appointments, if not managed appropriately, can accumulate into poor dental experiences and consequently, reinforce DFA into adulthood [11]. The long-term effects of these negative childhood dental experiences can lead patients to avoid seeking proper dental care in the future [12].

Pediatric dental patients with special health care needs (SHCN), such as patients with cancer, neurodivergent patients, or those with chronic conditions, including cardiovascular or pulmonary conditions or neurological afflictions, require extra time and special considerations during treatment due to medical, physical, cognitive, or developmental conditions [13]. This population includes children with behavior disorders (eg, autism spectrum, anxiety, and attention-deficit/hyperactivity disorder), congenital conditions (eg, trisomy 21 or congenital heart disease), developmental disorders (eg, cerebral palsy), systemic illnesses (eg, childhood cancer or sickle cell disease), or cognitive disabilities (eg, intellectual disability) [13]. Children with SHCN face more barriers to dental care than the overall population [13], including external factors like transportation, cost, inadequate dental facilities, as well as internal factors such as fear and poor tolerance [13,14]. Many children with SHCN are cared for by dentists in community settings or, more often, in hospital dental clinics [13]. They tend to experience a higher level of DFA, which can make dental visits more challenging [13]. Providing comprehensive care and ensuring each dental visit is positive for pediatric patients with SHCN is crucial in promoting good oral health habits and improving their oral health as they transition into adulthood [13]. Understanding and assessing DFA in children is key to delivering successful dental care with high satisfaction in this age group. Among the vast array of assessment methods available, self-report, parental proxy, observation-based, and physiological assessments are the four major types used to evaluate DFA in children [15]. Recently, salivary alpha-amylase, an enzyme linked to both adrenaline and noradrenaline, has also been used as a marker for autonomic nervous system activity and stress [16].

Factors in the dental setting that trigger DFA include loud dental instrument sounds, the presence of unfamiliar people examining the oral cavity, and fear of pain [17]. Of these, the biggest trigger of DFA is the anticipation and use of local anesthesia injections [9,17]. Although necessary for effective pain control during certain procedures, local anesthesia injections are understandably uncomfortable [9]. For children, the initial injection combined with the feeling of numbness during the procedure can be especially distressing [9]. Pharmacological agents, combined with light to moderate sedation or general anesthesia, can also be considered for noncooperative patients, who are often time-consuming and more costly and carry higher health risks [3]. In current research, audiovisual distractions such as tablets and TV screens have been used as additional distraction techniques beyond traditional tell-show-do methods, yielding overall positive results [18]. However, these techniques lack interactivity, resulting in less immersive distraction environments for children [19]. The lack of cooperation due to DFA often forces dentists treating pediatric patients to end appointments prematurely, sometimes without completing the planned procedures. Treating anxious and fearful patients can create a stressful environment for the clinician and the dental team [3]. Particularly when treating children with SHCN, extra time and tools are needed to ensure comfortable dental care. Depending on the child’s diagnosis, some may experience hypersensitivity to external stimuli such as loud noises, aversion to specific tastes, or difficulty straying from usual daily routines [20]. Furthermore, Pagano et al [20] showed that augmented reality was well suited for patients with autism spectrum disorder as preparation for their dental visits.

Additionally, a systematic review by Cunningham et al [21] concluded that virtual reality (VR) is a promising tool in dentistry, especially for children with autism spectrum disorder or other special health care needs. VR is defined as an artificial environment experienced through sensory stimuli [22]. It is a modern tool that immerses patients in a “game” or “virtual world.” Commonly used in medicine to distract patients during unpleasant procedures such as vaccination, cast removal, and short bedside interventions, VR has been proven effective at decreasing procedural anxiety and creating a more positive patient experience [23]. Limited existing research on VR in dentistry shows positive results for anxiety management during dental procedures. A recent clinical trial by Alshatrat et al [19] found that VR was effective in reducing anxiety in young children during dental procedures.

Additionally, a previous study by Ram et al [24] reported high satisfaction among both parents and clinicians using audiovisual glasses to guide children during dental treatments. However, research on clinical VR applications in pediatric dentistry remains limited, especially within populations with SHCN. VR offers potential as an additional nonpharmacologic tool for pediatric dentists. A clinical study assessing VR’s effectiveness during dental appointments in pediatric patients with SHCN could lead to better control of DFA and possibly facilitate easier procedures.

### The Study

#### Aims

The study aims to evaluate the efficacy of VR immersion as a tool in reducing anxiety in pediatric patients with SHCN undergoing dental procedures. The study also aims to gain insight into parents’ and health care providers’ satisfaction levels with the use of VR by children during dental treatments.

#### Hypothesis

We hypothesize that VR immersion will more effectively reduce anxiety in pediatric patients undergoing dental procedures than the standard intervention of watching a cartoon on a muted mounted TV set or tablet.

### Objectives

#### Primary Outcomes

The primary outcomes of this study are to measure both observed and objective biomarker-based indicators associated with DFA. The observed indicator will be evaluated using the Venham Anxiety Rating Scale (VARS) [25] (Table 1) and will be assessed by examining changes in mean levels of salivary alpha-amylase (SAA) between baseline (T0) and the middle of the intervention (T1) [26].

**Table 1. T1:** The Venham Anxiety Rating Scale.

Rating	Definition
0	Relaxed, smiling, willing, and able to converse.
1	Uneasy and concerned. During a stressful procedure, the child may protest briefly and quietly to indicate discomfort. Hands remain down or partially raised to signal discomfort. Child willing and able to interpret experience as requested. Tense facial expression, may have tears in eyes.
2	Child appears scared. Tone of voice and questions and answers reflect anxiety. During a stressful procedure, verbal protest, crying or quiet crying, hands tense and raised (not interfering much—may touch the dentist’s hand or instrument, but not pull at it). The child interprets the situation with reasonable accuracy and continues to work to cope with his or her anxiety.
3	Shows reluctance to enter the situation, difficulty in correctly assessing situational threat. Pronounced verbal protest and crying. Uses hands to try to stop procedure. Protest out of proportion to threat. Copes with the situation with great reluctance.
4	Anxiety interferes with the ability to assess the situation. General crying not related to treatment. More prominent body movements. The child can be reached through verbal communication, and eventually, with reluctance and great effort, he or she begins the work of coping with the threat.
5	The child is out of contact with the reality of the threat. General loud crying, unable to listen to verbal communication, and makes no effort to cope with the threat. Actively involved in escape behavior. Physical restraint required.

#### Secondary Outcomes

The secondary outcomes of this study are to compare the following indicators between the VR distraction and the standard intervention groups:

Parents’ (Multimedia Appendix 1) and health care professionals’ (Multimedia Appendix 2) satisfaction levelsChild satisfaction with the use of VR (Multimedia Appendix 1).Physiological parameters such as heart rate and oxygen saturationBehavior during the procedure (Table 2)Occurrence of side effectsLength of the dental procedureChild’s pain intensity (Multimedia Appendix 3)

**Table 2. T2:** The Venham Behavioral Rating Scale.

Rating	Definition
0	Total cooperation, best possible working conditions, and no crying or physical protest.
1	Mild or soft verbal protest, crying or quiet crying as a signal of discomfort, but does not obstruct progress. Appropriate behavior for the procedure, that is, slight start at injection, “ow” during drilling if hurting, and so on.
2	Protest more prominent. Both crying and hand signals. May move the head around making it hard to administer treatment. Protest is more distracting and troublesome. However, the child still complies with the request to cooperate.
3	Protest presents a real problem to the dentist. Complies with demands reluctantly, requiring extra effort by dentist. Body movement.
4	Protest disrupts procedure and requires that all of the dentist’s attention be directed toward the child’s behavior. Compliance was eventually achieved after considerable effort by the dentist, but without much actual physical restraint (may require holding the child’s hands or the like to start). More prominent body movement.
5	General protest, no compliance or cooperation. Physical restraint is required.

## Methods

### Design

This randomized controlled trial (RCT) will follow a parallel design with two groups: a control group (watching cartoons on a muted wall-mounted TV or a tablet) and an experimental group (VR intervention during the dental procedure).

### Sample and Setting

In mid-2023, we conducted a pilot study to evaluate feasibility and identify recruitment challenges before moving forward with the full RCT [27]. Between June 6, 2023, and July 20, 2023, 25 patients were recruited over 44 days at a single research site. Among these 25 patients, the mean VARS and Venham Behavioral Rating Scale scores before the procedure were 0.08 (SD = 0.28) for both scales, and during the procedure, the mean scores were 0.625 (SD = 1.35) and 0.667 (SD = 1.37), respectively. The variability in scores was higher at the time point with the higher average scores; therefore, we assumed a test with unequal variances. For the SAA outcome, data from a separate RCT conducted by our group were used [28]. This study measured changes in SAA before and during magnetic resonance imaging in children assigned to either a VR or a control condition. In that RCT, the mean difference in log-transformed SAA was 0.171 (SD = 1.05) in the control group and −0.096 (SD = 0.495) in the VR group. Because the expected difference in log SAA was smaller, this outcome guided our sample size calculations.

Therefore, to achieve 80% power to detect a mean difference of −0.096 (SD = 0.495) in log SAA using a 2-sided, 2-sample *t* test with unequal variances and a type-I error (α) of .05, a sample size of 364 participants (n=182 per group) was needed. Given the two primary outcomes, a Bonferroni correction was applied, reducing the α to .025. Based on an estimated 10% attrition rate from our pilot study, the final sample size was increased to 400 participants. Patients are currently being recruited for this study.

Recruitment is taking place at the dental clinic of the Centre Hospitalier Universitaire Sainte-Justine, a pediatric hospital in Montréal, Canada. This clinic mainly serves patients with SHCN, such as craniofacial abnormalities, autism spectrum disorder, or children battling cancer. Pediatric patients with SHCN make up about 80% of the clinic’s total clientele, while the remaining patients are otherwise healthy with dental trauma or other emergencies. The clinic sees roughly 5000 visits annually, including around 4000 patients with SHCN. Typically, about 600 (15%) of these patients have a severe diagnosis and are known to be completely uncooperative. Therefore, we estimate that approximately 3400 patients would be eligible for recruitment. Based on our pilot recruitment rate, we anticipate recruiting roughly 3 participants per week during September through April and 9 participants per week during May through August. Date collection is currently ongoing, and we expect to reach our target enrollment of 400 patients by the end of December 2025.

Participants will be identified by the clinic’s resident dentist using the scheduling system for upcoming appointments involving specific painful dental procedures, such as examinations, prophylaxis, extractions, and restorations. The research assistants will then contact the parents or legal guardians to provide information about the study and obtain their approval in advance. An independent individual, separate from the clinical dental team, will review the consent with both participants and parents. The information and consent form will be signed by a parent or legal guardian on the day of the visit. Whenever possible, patient assent will be sought.

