### Statistical Analysis

The primary analyses for this study will follow an intent-to-treat approach, using randomization status as the independent variable, and the mean difference in anxiety (using the anxiety subscale of the Venham) during the dental procedure (T1) and the SAA mean difference between T0 and T2 as the primary outcomes. As there are two primary outcomes (anxiety subscale and SAA), a Bonferroni correction will be applied, and a significance level of *P*=.025 will be used to determine statistical significance of primary outcomes. An ANCOVA, adjusting for unequal variances and adjusted for the time of the procedure, age, and baseline (T0) anxiety or behavioral score, will be used to assess the mean difference in Venham anxiety score during the dental procedure (T1) between the experimental and the control groups. An ANCOVA, adjusted for time of procedure, neurodevelopmental diagnosis, age, and baseline SAA level (T0), will be used to assess the mean difference in SAA level between groups 10 minutes after the procedure (T2).

For the secondary outcomes analyses, parametric tests adjusted for procedural type, age, sex, and parental presence will be used. Comparisons of dichotomous variables, including the necessity of procedural retakes, the use of other nonpharmacological interventions, and the occurrence of side effects, will be assessed using the Cochran-Mantel-Haenszel test. We will also perform subgroup analyses by age group (6‐12 y vs 13‐17 y) and sex and gender (boys, girls, or other) using ANCOVA. Any side effects will be reported using the Medical Dictionary for Regulatory Activities terminology [42], and their proportions will be compared between groups.

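### The reason for sizing on salivary alpha-amylase (SAA) does not bear on the Venham Anxiety Rating Scale (VARS), so the adequacy of 400 children for that primary outcome is not shown

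*Protocol article*

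**What the plan says.** Protocol article, Sample and Setting, gives two sets of planning figures.

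- **VARS**, from a pilot of 25 children not split by arm: "scores before the procedure were 0.08 (SD = 0.28) for both scales", the scales being the VARS and the Venham Behavioral Rating Scale. At the later rating, with the scales in that order: "during the procedure, the mean scores were 0.625 (SD = 1.35) and 0.667 (SD = 1.37), respectively".
- **SAA**, by arm, from a separate trial of VR during magnetic resonance imaging: "the mean difference in log-transformed SAA was 0.171 (SD = 1.05) in the control group", and a mean of −0.096 ("SD = 0.495) in the VR group").

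It then chooses the sizing outcome: "Because the expected difference in log SAA was smaller, this outcome guided our sample size calculations". The result is 182 per group, raised to 400 in total for 10% attrition.

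Under Statistical Analysis, an ANCOVA "will be used to assess the mean difference in Venham anxiety score during the dental procedure (T1") between the two arms. Because there are two primary outcomes, "a Bonferroni correction will be applied", so each is tested at .025 whatever the result of the other.

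**The concern.** Sizing on one of two primary outcomes is sound if that outcome needs the larger sample. Required sample size depends on the between-arm difference divided by its SD. The stated reason compares quantities that cannot be ranked, on two counts:

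- **Units.** One is in log enzyme activity, the other in points of a six-level scale.
- **Kind.** The SAA figure contrasts VR with control. The VARS figure contrasts two time points in one pooled sample and is not a treatment effect.

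No between-arm VARS difference, sample size or power appears anywhere in the article. A reader will take it that 400 children suffice for both primary outcomes, and only SAA has been checked. If VARS comes out non-significant, nothing in the plan says which effects the trial could have detected, and the result may be misread as no effect.

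**Working it through.** **1. The plan's own figure.** Inputs: SAA change 0.171 (SD 1.05) in control and −0.096 (SD 0.495) in VR; 80% power; two-sided unequal-variance t test.

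- Difference: 0.171 − (−0.096) = 0.267.
- n per group ≈ (z₁₋α/₂ + z₀.₈)² × (SD₁² + SD₂²) / difference².
- At alpha .025: (2.241 + 0.842)² × (1.05² + 0.495²) / 0.267² ≈ 180. The exact Welch (noncentral t) calculation gives **182**.
- At alpha .05 the Welch calculation gives 150.

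So 182 reproduces, with alpha .025 and a difference of 0.267. The sentence reporting it instead cites alpha .05 and a difference of −0.096 (SD 0.495), which does not give 182. That wording should be corrected together with the point made here.

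**2. Standardising what the article gives.**

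| Quantity | Difference | SDs | Standardised | n per group, alpha .025 |
|---|---|---|---|---|
| SAA, VR vs control | 0.267 | 1.05, 0.495 | 0.325 | 182 |
| VARS, before vs during | 0.625 − 0.08 = 0.545 | 1.35, 0.28 | 0.56 | 64 |
| VARS, before vs during | 0.545 | 1.35, 1.35 | 0.40 | 118 |

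The standardised difference uses the root mean square of the two SDs. If 0.545 were the between-arm effect, SAA would be the limiting outcome. But 0.545 is 0.545/0.625 = 87% of the mean during the procedure. Using it as a treatment effect assumes that VR returns children to their score before the procedure.

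**3. What the trial can detect on VARS.** Analysed sample: 400 × 0.9 = 360, or 180 per group. Detectable difference ≈ (2.241 + 0.842) × √((SD₁² + SD₂²)/180).

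- SD 1.35 in both arms: 3.083 × √(3.645/180) = 0.439; Welch **0.44 points**.
- VR SD 0.95 (about 1.35 × √0.5, the SD shrinking with the square root of a halved mean): 3.083 × √(2.725/180) = 0.379; Welch **0.38 points**.

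**4. Power by size of effect.** This assumes that 0.625 (SD 1.35) is the control value, which the article does not state. 180 per group, alpha .025, Welch:

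| VR reduction | Difference | Power, SD 1.35 in both arms | Power, VR SD shrinking with √mean |
|---|---|---|---|
| 40% | 0.250 | 31% | 39% |
| 50% | 0.3125 | 48% | 61% |
| 60% | 0.375 | 65% | 81% |
| 70% | 0.4375 | 79% | 94% |

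VARS needs more children than SAA only if the true reduction is below about 70% (equal SDs) or 60% (shrinking SD).

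**5. Holm in place of fixed Bonferroni.** The smaller p value is tested at .025 and, if significant, the other at .05. For a halving with SD 1.35 in both arms, VARS power at .05 is 59% against 48% at .025. The 59% is an upper bound, reached only when SAA succeeds.

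**6. Mean-based or ordinal test.** The value 0.625 = 15/24 suggests 24 children rated during the procedure. Only four sets of integer 0 to 5 scores give that mean with SD 1.35, and they contain 18 or 19 zeros (75% or 79%). Simulated power at 182 per group, alpha .025, on a control distribution averaged over those four:

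| Effect of VR | Welch | Wilcoxon |
|---|---|---|
| None (type I error) | 2.4% | 2.4% |
| Half of non-zero children move to 0 | 63% | 75% |
| Proportional odds, OR 0.5 | 54% | 61% |
| Every non-zero score falls one level | 35% | 26% |
| Only scores 3 to 5 fall, to 1 | 90% | 6% |

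The mean-based test holds its level, and neither test is better throughout.

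**The case against.** The strongest reply is that the choice of SAA may be right even though the reason is poorly put. The article does not say that raw differences were compared. Once standardised, the only VARS difference it reports (0.40 to 0.56) is larger than the SAA difference (0.325) and needs 64 to 118 per group against 182. A detectable 0.44 points with SD 1.35 is 0.33 SD, about the same standardised sensitivity as for SAA. The low power for a halving rests on treating 0.625 as a control value. The pilot is not split by arm, and the Experimental Intervention section cites it for the headset not hindering procedures, so some pilot children probably wore one.

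Much of this stands. A reader might infer that VARS is the weaker primary outcome on the pilot figures, or that the trial could see only a very large VARS effect. The documents support neither, because they fix no between-arm VARS effect. A reader might also infer from the many zeros that the ANCOVA wastes power. The simulations do not bear that out, because the ordering of the tests depends on which children VR helps. Bonferroni is valid and consistently stated, so Holm improves the plan and corrects no error.

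What does not stand is using 0.545 to defend the ranking. It is a change over time in a pooled sample, so the case that VARS is covered remains unmade.

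**Conclusion.** The point holds in a limited form. The stated reason for sizing on SAA sets a between-arm log-SAA difference against a pooled before-to-during VARS change in other units. With no between-arm VARS effect or power given, the adequacy of 400 children for VARS is not shown. At 180 per group and alpha .025 the trial detects about 0.38 to 0.44 VARS points with 80% power, depending on the VR SD.

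Whether that is enough is open. VARS would be the weaker outcome only if 0.625 (SD 1.35) approximates the control value and VR lowers it by less than about 60% to 70%. These calculations are unadjusted, like the plan's own; covariate adjustment could help, but the article gives no correlation from which to judge by how much.

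**What to change.** 1. In Sample and Setting, replace the sentence on the smaller difference with the detectable between-arm VARS difference at 80% power, alpha .025 and 180 per group: about 0.44 points if the SD is 1.35 in both arms, about 0.38 if the VR SD is 0.95. State that the SD of 1.35 comes from a pilot not split by arm.
2. In Statistical Analysis, replace fixed Bonferroni with Holm: the smaller p value at .025 and, if significant, the other at .05.
3. Keep the mean-based ANCOVA as the primary VARS test. An ordinal analysis with the same covariates may be added as a sensitivity analysis.

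The cost is wording and one testing rule; recruitment and data collection are untouched. With 300 of 400 children recruited, and with staff, participants and parents unblinded, the Holm rule should be dated and recorded before any comparison by arm. Leaving the primary VARS model unchanged avoids a late switch of a stated primary test in an open-label trial.

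### The sample-size statement names the wrong detectable difference and the wrong alpha: 182 per group follows from a between-group log-SAA difference of 0.267 at alpha .025, not from −0.096 at .05

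*Protocol article*

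**What the plan says.** All the inputs stand in the section Sample and Setting. For the SAA outcome the authors use their earlier MRI trial, in which "the mean difference in log-transformed SAA was 0.171" (SD 1.05) in the control group and −0.096 (SD 0.495) in the VR group. SAA is said to have guided the sample size. The calculation is then stated as the number required "to achieve 80% power to detect a mean difference of −0.096" (SD 0.495), "using a 2-sided, 2-sample *t* test with unequal variances and a type-I error (α) of .05", with the result that "a sample size of 364 participants (n=182 per group) was needed".

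The next sentence adds: "Given the two primary outcomes, a Bonferroni correction was applied, reducing the α to .025". It does not say whether 364 was obtained before or after that step. The attrition step follows: "Based on an estimated 10% attrition rate from our pilot study, the final sample size was increased to 400 participants". The Statistical Analysis section confirms the threshold that will be applied: "a significance level of *P*=.025 will be used to determine statistical significance of primary outcomes".

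**The concern.** A two-sample t test compares two arms, so its target must be a difference between arms. The value −0.096 is the change within one arm. The sentence is also inconsistent in itself: it names an unequal-variance test but gives only one SD. As printed, 364 is attached to alpha .05 and the Bonferroni step comes afterwards, so a reader cannot tell whether the trial was sized for two primary outcomes.

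At stake is the power claim for a primary outcome. The paper claims 80% power for an effect about 2.8 times smaller (0.267 / 0.096) than the one the sample size supports. Anyone who reads a null SAA result against the planned power would credit the trial with far more sensitivity than it has.

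**Working it through.** **Inputs** (all from Sample and Setting)
- Control change +0.171, SD 1.05; VR change −0.096, SD 0.495.
- Equal allocation, two-sided test, 80% power, alpha .05 as printed or .025 after Bonferroni.
- Stated result: 182 per group, 364 in total; 10% attrition; 400 enrolled.

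**Method.** Welch t test with n per group: SE = √[(s₁² + s₂²)/n], Satterthwaite degrees of freedom, noncentrality = difference/SE, power from the noncentral t distribution. As a check, the normal approximation is n = (z₁₋α/₂ + z₀.₈)² (s₁² + s₂²)/difference².

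**Step 1: the calculation as printed.** Difference 0.096, SD 0.495 in both arms, alpha .05:
- Normal approximation: (1.960 + 0.842)² × (2 × 0.245025)/0.009216 gives 418 per group. The t test gives 419.
- This is more than twice the stated 182.

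**Step 2: other readings of the printed target (0.096).**

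| SDs | alpha | n per group needed | power at 182 per group |
|---|---|---|---|
| 0.495 / 0.495 | .05 | 419 | 45% |
| 0.495 / 0.495 | .025 | 507 | 35% |
| 1.05 / 0.495 | .05 | 1,149 | 20% |
| 1.05 / 0.495 | .025 | 1,392 | 13% |

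A one-sided .05 test needs 329 per group, and a one-sample or paired calculation at .05 needs 209. None of these gives 182.

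**Step 3: the between-group difference.** 0.171 − (−0.096) = 0.267, with SDs 1.05 and 0.495:
- s₁² + s₂² = 1.1025 + 0.245025 = 1.347525.
- At n = 182, SE = √(1.347525/182) = 0.0860 and noncentrality = 0.267/0.0860 = 3.10, with about 258 degrees of freedom.
- At alpha .025 the critical value is 2.255 and power is 80.1%. With 181 per group it is 79.9%, so 182 is the smallest n that reaches 80%. The normal approximation gives 180.
- At alpha .05 the same inputs need only 150 per group, and 182 would give 87%.

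The plan's figure is therefore reproduced exactly by 0.267, both arm SDs and alpha .025. The Bonferroni correction is already inside the 364.

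**Step 4: attrition.**
- 364 × 1.10 = 400.4, which matches the stated 400.
- To retain 364 after 10% loss, 364/0.90 = 404.4, so 405 (406 for equal arms).
- 400 × 0.90 = 360, or 180 per group. Power for 0.267 at .025 is then 79.7%.

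**The case against.** The strongest reply is that nothing in the trial has to change. The sample size is right for the difference that the source data imply, at the alpha that will be used, and both arms' means and SDs are printed just before the faulty sentence, so a careful reader can recover 0.267. That is true, and it is why the remedy is confined to wording. It does not make the printed claim correct.

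A second reply is that 13% to 20% is the worst case, because the faulty sentence gives only SD 0.495; taken literally, power is 35% to 45%. This is fair, and both ranges should be given. The lower one uses the two arm SDs that the document reports and that an unequal-variance test calls for. Neither is near 80%.

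Third, the alpha point is partly sentence order, since .025 is stated in the very next sentence and again in Statistical Analysis. No threshold used in the analysis is wrong; only the alpha attached to 364 is.

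Fourth, the attrition slip is about 1% of the sample, and the planned ANCOVA could recover it: if the covariates had a multiple correlation of only 0.1 with the outcome (an assumption), 180 per group would already give 80.1%. This stands, and the attrition line should not be counted as a serious error.

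Finally, 0.267 is never printed as the target. It is inferred, so the sponsor should confirm it.

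**Conclusion.** The concern holds. The stated detectable difference for a primary outcome is one arm's change, and the stated alpha is not the one under which 364 was obtained. With 182 per group, power for a true difference of 0.096 is 13% (alpha .025) to 20% (alpha .05) under SDs 1.05 and 0.495, or 35% to 45% under SD 0.495 in both arms, against the 80% claimed. For 0.267 at .025 it is 80.1%, or 79.7% once 10% attrition from 400 is allowed for.

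These figures assume an unadjusted Welch t test, equal arms, and that the MRI trial's means and SDs carry over to the dental setting. That 0.267 at .025 was the basis actually used is an inference from an exact match. The paragraph must be corrected because its power claim is false as printed, although the sample size needs no revision.

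**What to change.** After the sponsor confirms the basis, replace the calculation sentence with wording such as: *182 participants per group (364 in total) give 80% power, with a two-sided Welch t test at alpha .025 (Bonferroni for two primary outcomes), to detect a between-group difference of 0.267 in the change in log SAA (control +0.171, SD 1.05; VR −0.096, SD 0.495).*

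Delete the mention of alpha .05 and fold the Bonferroni sentence into this one. For attrition, either state 405 enrolled (406 for equal arms), or keep 400 and state that 10% attrition leaves 360 evaluable participants and 79.7% power.

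If 400 is kept, the cost is wording only: no change to recruitment, the analysis or the significance threshold. With 300 recruited as of November 2025 and results expected in June 2026, the correction can be on record before results are reported, which avoids any appearance that the target was redefined afterwards.
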